## Abstract

**Background**: Radiation therapy with or without systemic treatment for lung cancer can cause adverse reactions, e.g., fatigue. Affected patients may experience a decrease in physical activity and, as a consequence, be unable to receive the complete assigned treatment. Physical exercise may be helpful. A benefit of exercise regarding completion of systemic treatment and quality of life was previously suggested. Irradiated patients may benefit as well. A smartphone-based app reminding patients to make a minimum number of steps might positively influence physical activity. The prototype of an app called “Step Reminder” was recently finalized. The randomized APPAREL trial (NCT07627022) evaluates whether this app can improve physical activity during irradiation for lung cancer. **Methods**: The primary endpoint of this phase 2 trial focuses on the within-patient change regarding the mean number of daily steps (week 5 minus week 1). Secondary objectives include satisfaction with the application and its impact on the perception of digital health technology. Patients are randomized 1:1 to be treated with a standard approach (conventionally fractionated irradiation with or without systemic treatment) supported by the “Step Reminder” app (Arm A) or standard treatment without the app (Arm B). The app provides reminders several times per day to walk a pre-defined number of steps. To make sure that the required 28 patients are included in the primary analysis population (full analysis set), 32 patients have to be randomized. **Results**: At this stage, results are not available. **Conclusions**: It is expected that the app will have a positive effect on the patients’ physical activity (number of steps).

## 1. Introduction

Conventionally fractionated radiation therapy is a frequently applied treatment for non-small-cell (NSCLC) or small-cell (SCLC) lung cancer [1,2]. This type of treatment might cause side effects within the radiation field or general symptoms such as fatigue, resulting in a decreased level of physical activity or function [3,4,5,6,7,8]. In case of more severe treatment-related side effects, the patients may be unable to receive the complete treatment they have been assigned to. Maintaining or improving the level of physical activity by any kind of physical exercise may be of benefit.

Such an effect was shown for cancer patients receiving neoadjuvant chemotherapy, of whom 16.8% (31 patients) had lung cancer [9]. Patients undergoing an exercise program could receive chemotherapy more frequently. In other studies, physical activity resulted in improvement of quality of life in patients with lung cancer [10,11,12,13,14,15,16,17,18]. In a retrospective study of 50 patients receiving chemotherapy for advanced or recurrent lung cancer, a lower level of activity was negatively associated with survival [19]. According to these studies, physical activity appears important for patients treated for lung cancer. Exercise programs can be challenging for the patients, particularly if their well-being is affected by fatigue or other adverse reactions [20,21].

It would be interesting to know whether, in addition to or as an alternative to in-person group training programs, a mobile application that reminds patients to walk a certain number of steps will have a positive impact on physical activity. The prototype of a corresponding app called “Step Reminder” was recently finalized. This randomized phase 2 trial (APPAREL) is going to evaluate whether the “Step Reminder” app can help improve physical activity during a series of radiation therapy with or without systemic treatment administered for locally advanced lung cancer. Improvement is defined as a reduction in the difference in the average number of daily steps (week 5 minus week 1) during the period of radiation treatment.

## 2. Materials and Design

### 2.1. Objectives

The primary objective is the exploration of whether the “Step Reminder” app will lead to alteration of the physical activity during a course of irradiation. The primary endpoint is the within-patient alteration of physical activity, given by the weekly average number of steps per wear-hour of the smartphone, between week 1 and week 5. Study groups A and B are compared to identify potential differences due to the support of the “Step Reminder” app. This endpoint represents a normalized activity metric and is commonly applied in digital health studies to account for heterogeneity in device usage and to reduce bias associated with unequal observation periods across patients [22]. It is a behavioral digital activity endpoint selected because the intervention directly aims to maintain or increase physical activity during radiotherapy. It is not considered a validated surrogate endpoint for treatment completion, toxicity reduction, quality of life, or survival. The potential clinical relevance is supported indirectly by prior studies suggesting associations between physical activity/exercise and quality of life, treatment tolerance, hospitalization risk, and prognosis in lung cancer and other oncology populations; however, causal conclusions on these outcomes are beyond the scope of the present protocol. Secondary objectives include patient satisfaction with the “Step Reminder” app and the potential influence of using this app on the patient’s attitude towards digital health technology (assessed at the end of week 5). Furthermore, exploratory analyses investigate whether the observed effects are different between baseline characteristic-related subgroups. Due to the limited sample size, these analyses can only help to generate hypotheses and inform the design of future studies.

### 2.2. Design and Duration

This is a multicenter prospective randomized study (phase 2) in patients irradiated for lung cancer. Patients are randomized 1:1 and receive standard irradiation and the “Step Reminder” app (Arm A) or standard irradiation without the “Step Reminder” app (Arm B). “Step Reminder” is a smartphone-based application that provides three or four reminders per day (patient’s selection) to motivate the patients to walk a pre-defined number of steps each day. Randomization will be stratified by concurrent systemic therapy [23].

Physical activity is going to be assessed at previously defined time points during the period of radiation therapy, i.e., during week 1 and week 5, using step count data from an integrated step counter of the smartphone or a stand-alone device. The recruitment of the required 32 patients will be finalized within 6 months. Each patient will stay in the study for the radiotherapy course, which takes 5–7 weeks. Thus, overall study time is expected to be 8 months.

The criteria required to qualify for inclusion in the APPAREL trial include lung cancer (confirmed by pathology), treatment with at least 50 Gy of conventionally fractionated radiation therapy, and availability of a smartphone with an already integrated step counter or a smartphone supplemented by a corresponding health app. Patients must be 18 years or older and provide written informed consent. Patients unable to consent or giving the impression of insufficient compliance may not be included.

Patients can terminate their participation in the trial at any time without negative consequences. Participation may be stopped prematurely by the principal investigator if reasonably justified. In this situation, the affected patient and the ethics committee will be informed promptly.

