#### 2.4.1. Radiation Therapy

Patients receive a standard treatment for lung cancer according to the current German guideline [2]. For patients with inoperable locally advanced NSCLC, the treatment often includes fractionated radiation therapy with total doses of 66–70 Gy (dose per fraction = 2.0 Gy) conventionally. It may be combined with concurrent chemotherapy. Depending on the histologic subtype, cisplatin is combined with vinorelbine (squamous cell carcinoma), pemetrexed (adeno-carcinoma), or paclitaxel (both subtypes), followed by consolidation therapy with durvalumab [2]. Some patients with SCLC may be irradiated with daily fractions of 2.0 Gy up to 60–66 Gy. For these patients, radiation treatment is generally combined with four to six courses of chemotherapy, of which two courses are given concurrently. Standard chemotherapy for SCLC includes cisplatin and etoposide [2]. For patients not experiencing progression during radio-chemotherapy, consolidation systemic treatment with durvalumab may be offered. Irradiation may be associated with acute or subacute side effects, which may cause an interruption of the treatment. If the next radiation fraction is delayed for more than 7 days, the principal investigator has to be notified.

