### 2.5. Statistics

#### 2.5.1. Sample Size

This prospective randomized study is designed to analyze the effect of the “Step Reminder” app on physical activity during irradiation in lung cancer patients. The primary endpoint is the within-patient change in weekly average steps per wear-hour between the fifth and the first week. The primary analysis includes all randomized patients with evaluable data regarding the primary endpoint. The comparison (“Step Reminder” app group vs. control group) is made with a two-sided Wilcoxon–Mann–Whitney U test.

Calculation of the required sample size considers a clinically relevant difference corresponding to a relative difference in the within-patient change in steps per wear-hour of about 30% between treatment arms. Given the non-parametric nature of the primary analysis, this assumption is interpreted as a moderate shift in the distribution of the endpoint, which represents a probability of superiority of about 0.65. The assumed 30% relative difference represents a pragmatic planning assumption for this exploratory randomized phase 2 trial and should not be interpreted as an established minimal clinically important efficacy difference for this endpoint. Assuming a two-sided significance level of α = 0.05 and a statistical power of 80%, 28 patients are needed to detect such an effect using the asymptotic approximation of the Wilcoxon–Mann–Whitney U test. It is assumed that approximately 10% of the randomized patients cannot be evaluated with respect to the primary endpoint. Therefore, 32 patients need to be randomized. The calculation aligned with the analysis population, and the endpoint definition is considered appropriate for this exploratory study. The multicenter design primarily supports recruitment feasibility and broader applicability of the exploratory findings; it is not intended to imply a confirmatory multicenter efficacy trial. Results are interpreted descriptively and will contribute to the design of additional larger studies.

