#### 2.5.3. Statistical Aspects Related to the Primary Endpoint

Primary analysis is performed in the full analysis set and compares the distribution of within-patient changes between the treatment groups (“Step Reminder” app vs. control). No imputation of missing data is performed. The analysis is based on observed cases only. Extent and pattern of missing data are described descriptively. The primary estimand is directed at the difference between treatment groups in the average within-patient change in physical activity between the fifth and the first week. Intercurrent events, including incomplete smartphone use, technical failures, or treatment interruptions, are addressed using a treatment policy strategy, where available, valid data are included without imputation. Descriptive statistics of the primary endpoint will be provided by treatment group, including the number of subjects with evaluable data, mean (plus standard deviation), and median (plus quartiles, minimum, and maximum). Individual patient trajectories are visualized using spaghetti plots. The endpoint represents a normalized activity metric and is intended to account for heterogeneity in device usage and to reduce bias associated with unequal observation periods. Wear-time has been shown to influence estimates derived from consumer-grade wearable data, supporting the need to account for device usage time in digital physical activity analyses.

The primary comparison between treatment groups is performed with the two-sided Wilcoxon–Mann–Whitney U test. The magnitude of the treatment effect is estimated using the Hodges–Lehmann estimator together with a two-sided 95% confidence interval. Given the limited sample size, the results are interpreted descriptively only. A paired *t*-test may be reported as an additional analysis if the distribution of within-patient differences is approximately normal.

Within each treatment group, the change between week 1 and week 5 is analyzed using the Wilcoxon signed-rank test. A paired *t*-test may be provided as a supportive analysis if appropriate. If diagnostic checks indicate substantial skewness, a supportive analysis on the log scale is performed, and results are expressed as ratios of geometric means with corresponding 95% confidence intervals, without changing the primacy of the analysis on the original scale.

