## Figures and Tables

**Table 1 jcm-15-05678-t001:** Assessments at the time of screening, at baseline, and during radiation therapy.

	Screening	Baseline	End of Week 1 of Radiation Therapy	End of Week 5 of Radiation Therapy
Demographics	X			
Medical history and medication		X	X	X
Patient and tumor characteristics		X		
Performance status		X	X	X
Assessment of distress		X		
Assessment of pain		X		
Assessment of fatigue		X		
Details of radiation therapy	X			
Radiation therapy performed as planned?			X	X
Written informed consent given	X			
Fulfillment of inclusion criteria	X			
Expected non-compliance	X			
Wear-time of the smartphone			X	X
Number of steps per day			X	X
Handling smartphones		X		
Satisfaction with the “Step Reminder” app				X
Influence of using health technology				X

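### Step measurement is tied to the radiotherapy course, which appears to leave patients who stop before week 5 without a primary endpoint value and is not reconciled with the treatment policy strategy

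*Protocol article*

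**What the plan says.** Section 2.2 sets the length of participation: "Each patient will stay in the study for the radiotherapy course", given there as 5-7 weeks. The same section says that activity is "assessed at previously defined time points during the period of radiation therapy, i.e., during week 1 and week 5". Table 1 labels its last column "End of Week 5 of Radiation Therapy" and lists nothing after it. Section 2.5.1 defines the primary endpoint as the "within-patient change in weekly average steps per wear-hour between the fifth and the first week".

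On what happens when radiotherapy does not run to plan, Section 2.5.3 lists incomplete smartphone use, technical failures, "or treatment interruptions, are addressed using a treatment policy strategy, where available, valid data are included without imputation". Section 2.5.2 restricts the primary analysis to patients with valid data in both weeks and rules out imputation and missing-data sensitivity analyses.

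The article expects such events. The Introduction notes that more severe side effects may keep patients from completing their treatment. Section 2.4.1 says that side effects may interrupt radiotherapy, and adds: "If the next radiation fraction is delayed for more than 7 days, the principal investigator has to be notified". No rate of interruption or early stopping is given.

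**The concern.** A treatment policy strategy asks for the outcome at the planned time regardless of the intercurrent event, so it works only if the outcome is still collected after the event. Here participation and measurement are both described as lasting for the radiotherapy course. If the course ends in week 3 or 4, the wording leaves no point at which week-5 steps would be collected, and the complete-case rule then removes the patient.

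The patients lost this way are selected by something that happens after randomisation and is plausibly related to toxicity, and so to activity. The trial's own rationale is that activity may help patients complete treatment, so stopping could also differ between arms. Even with equal loss in both arms, the comparison would describe change among patients still on radiotherapy in week 5. That is narrower than the estimand in Section 2.5.3. With no imputation and no sensitivity analysis planned, a value that was not collected cannot be made up for later.

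**Working it through.** **The provisions side by side**

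| Question | What the article provides | Where |
|---|---|---|
| How long is a patient in the study? | For the radiotherapy course | Section 2.2 |
| When are steps measured? | Weeks 1 and 5, within the radiotherapy period | Section 2.2, Table 1 |
| Is there a later visit? | No | Table 1 |
| Who enters the primary analysis? | Patients with both weeks valid; no imputation | Section 2.5.2 |
| How are treatment interruptions handled? | Treatment policy, using available valid data | Section 2.5.3 |
| Are steps collected after an early stop? | Not stated | - |

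The first four rows together yield no week-5 value after an early stop. The fifth row presupposes one. The limit to available data does not close the gap, because the follow-up wording is what would make the data unavailable.

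**How early a stop has to be**

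Inputs: planned dose of at least 50 Gy (Section 2.2); 2.0 Gy per fraction and totals of 60-66 Gy or 66-70 Gy (Section 2.4.1). Two assumptions are mine: five fractions a week, and 2.0 Gy also at the 50 Gy minimum.

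- Fractions = dose / 2.0, and weeks = fractions / 5.
- 50 Gy: 25 fractions, 5.0 weeks. 60 Gy: 30 fractions, 6.0 weeks. 66 Gy: 33 fractions, 6.6 weeks. 70 Gy: 35 fractions, 7.0 weeks.
- Week 5 is fractions 21-25. It is lost entirely if the course ends by fraction 20, that is, with the last 25 - 20 = 5, 30 - 20 = 10, 33 - 20 = 13 or 35 - 20 = 15 fractions not given.

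At the 50 Gy minimum the course ends exactly with week 5, so any early stop falls before the window closes. At 60-70 Gy, only a stop that omits at least 10 to 15 fractions removes the whole week.

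**What a pause does**

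After a one-week pause earlier in the course, calendar days 29-35 contain fractions 16-20 (32-40 Gy). The fifth week of delivered treatment is then days 36-42, with fractions 21-25 (42-50 Gy). The two counts differ only if weeks of delivered treatment are meant.

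**The allowance for non-evaluable patients**

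The plan's own inflation step reproduces: 28 / 0.90 = 31.1, and the plan randomises 32. The allowance is 32 - 28 = 4 patients, and the expected number evaluable is 32 x 0.90 = 28.8. I take 28 as the plan's target, since this point does not depend on how it was derived.

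If a further share e loses week 5 through early stops on top of the 10%, the expected number evaluable is 32 x 0.90 x (1 - e). The number to randomise for 28 evaluable is 28 / (0.90 x (1 - e)), rounded up. The values of e are assumptions.

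| e | Expected evaluable of 32 | To randomise for 28 |
|---|---|---|
| 0% | 28.8 | 32 |
| 5% | 27.4 | 33 |
| 10% | 25.9 | 35 |
| 15% | 24.5 | 37 |
| 20% | 23.0 | 39 |

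If the 10% already covers early stops, the first row applies. The count is then unaffected, but the selection remains.

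**The case against.** The case on the other side is substantial. The sentence in Section 2.2 feeds the overall timeline and is not an exit rule. The same section describes early exit separately, by the patient's choice or by a justified decision of the principal investigator, and does not list stopping radiotherapy. Table 1 asks at the end of week 5 whether radiotherapy went as planned, so the visit is evidently meant to take place when it did not. Section 2.4.2 takes phone data for weeks 1 and 5 without requiring that radiotherapy be ongoing. Section 2.5.2 uses all available data irrespective of adherence to the assigned treatment. Section 2.5.3 names interruptions, not permanent stops. The Discussion already concedes attrition bias and possibly non-random missing data.

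Much of this stands. A reader might infer that the protocol withdraws patients who stop radiotherapy, or that it openly contradicts its estimand. No sentence says either; the loss is an inference from wording about duration. A reader might also infer that a pause shifts week 5. That requires counting weeks of delivered treatment, which the article nowhere states, and Sections 2.5.1, 2.5.2 and 2.5.3 read more naturally as weeks since the start of radiotherapy. An exact day window may well be in the full protocol.

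The gap around early stops remains. The adherence clause in Section 2.5.2 gives only the app as its example, and no passage provides for step collection once radiotherapy has ended. Disclosing attrition bias is not a reason to accept a part of it that can be avoided.

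**Conclusion.** The point holds as an unreconciled pair of provisions: measurement tied to the radiotherapy course, and a treatment policy strategy that needs measurement whatever happens to treatment. It should be resolved, but it is not an explicit contradiction. The calendar definition of week 5 for paused patients is a clarification and not a separate error.

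The size is open. The documents give no rate of early stops and do not say what the 10% allowance covers, so the effect on the number evaluable runs from none to the assumed losses tabulated above. The direction of any bias cannot be determined from the documents. That the loss is related to toxicity and activity is plausible but not shown there.

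**What to change.** In Section 2.2 and Table 1, count calendar time from the first fraction and define week 5 as days 29-35. State that steps and wear-time for that window are collected from every randomised patient who has not withdrawn consent, whether radiotherapy is ongoing, paused or stopped, and that participation lasts at least to day 35. The carrying instruction in Section 2.4.2 should apply to the end of that window.

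The cost is small. The phone records the steps anyway, so a patient who has stopped needs one data extraction and no new procedure. Day 35 lies within the stated 5-7 weeks, so the planned 8-month duration need not change.

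There is a downside. For stopped or paused patients, week 5 will reflect less delivered radiotherapy. In Arm A it may also fall in a period without reminders, because Section 2.4.3 ties these to the radiotherapy course; the protocol should say what applies. A treatment policy estimand accepts both, and they can be described by arm with the existing Table 1 item on whether radiotherapy went as planned.

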### 2.3. Registration and Randomization

The patient code consists of the number of the contributing center (one digit), followed by a letter for the treatment approach (R = radiotherapy alone, S = radiotherapy plus systemic treatment) and a consecutive number consisting of 3 digits. Example: 1R-001.

Patients will be randomized 1:1 to receive either standard treatment for lung cancer supported by the “Step Reminder” app (Arm A) or standard treatment for lung cancer without the app (Arm B) using a block randomization scheme. Randomization is stratified according to presence or absence of concurrent systemic therapy (yes vs. no) [23]. The randomization list is going to be provided by an external professional statistician. The information regarding randomization (Arm A or Arm B) will be obtained from the department of the principal investigator. Study personnel will provide standardized instructions regarding smartphone handling to all participants to ensure consistent data collection conditions across study sites.

### 2.4. Procedures

Data assessed prior to radiation therapy include medical history, medication, demographics, body mass index, Karnofsky performance score, National Comprehensive Cancer Network (NCCN) distress thermometer (including physical, emotional, social, practical, and spiritual or religious concerns [24,25]), pain score (patient self-assessment, points from 0 to 10), fatigue (patient self-assessment, points from 0 to 10), tumor histology, tumor stage, systemic treatment, parameters of the planned radiation therapy, and the number of daily reminders (three or four) the patient has chosen. Assessments performed at the time of screening, at baseline, and during radiation therapy are given in Table 1.

